### Recruitment

The clinical investigators will be trained on comprehensive assessment of inclusion, exclusion and withdrawal criteria. Every patient diagnosed with gastric cancer in the hospital will be screened for qualification. The investigators will communicate with potential participants and their relatives. In this way, potential participants will be recruited professionally. Recruitment progress will be monthly summarized and reported to the trial director to ensure sufficient recruitment of participants. The expected recruitment rate is 20–22 participants per month, and the recruitment progress is expected to last for 2 years.

### Randomization

Participants will be randomized into dual tracer, ICG, CNs, or control (non-tracing) group. A random digit table is used for randomization as follows: (1) according to the order of inclusion, each participant will be allocated a random number, and (2) divide the number by 4. If the remainder is 0, the participant will be enrolled into dual tracing group. If the remainder is 1, the participant will be enrolled into non-tracing group. If the remainder is 2, the participant will be enrolled into CNs group. If the remainder is 3, the participant will be enrolled into ICG group. The allocation is not blinded to surgeons or participants before performing procedure.

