## Methods

### Study design

This is a prospective, unblinded, superiority testing, randomized controlled trial. A parallel group cluster randomized controlled trial with four arms will be conducted. Figure 1 demonstrates the flow chart of current study. Figure 2 contents the schedule of enrolment, interventions, and assessments. Participants were randomized into 4 groups at a 1:1:1:1 ratio: (1) control group: participants will undergo conventional laparoscopic radical gastrectomy without any tracer; (2) ICG group: participants will undergo laparoscopic radical gastrectomy with subserosal ICG navigation; (3) CNs group: participants will undergo laparoscopic radical gastrectomy with submucosal CNs navigation; (4) dual tracer group: participants will undergo laparoscopic radical gastrectomy with both tracers, i.e., subserosal ICG and submucosal CNs. Primary and secondary outcomes will be assessed after the gastrectomy. The study protocol is reported in accordance with the guidelines outlined in the SPIRIT Checklist for Trials (Additional file 1) [16].

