### Sample size

This study is a superiority testing trial (one-tailed trial) of which the primary outcome is the number of retrieved LNs and study subjects will be divided into 4 groups. Combined with our previous findings and literature reports, the standard deviation σ of the total number of LNs in control group was 8.6 [9, 13, 17]. The *α* (test level) is set as 0.05 and power (1-β) is 0.8. A difference of more than 3 in the total number of detected LNs will be considered as significant, i.e., the effect value *d* = 3/*σ* = 0.35. Thus, at least 103 (102.3) participants are required in each group. Considering an expected dropout rate of 20%, 129 (128.75) participants are finally required in each group, leading to a total of 516 participants.

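### The remainder-of-4 rule secures 1:1:1:1 only on average and only for a number range that is not stated, leaves procedure type to chance, and sits beside a mistaken cluster label

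*Protocol article*

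**What the plan says.** The Randomization section sets out the allocation step by step. "A random digit table is used for randomization as follows": "according to the order of inclusion, each participant will be allocated a random number", that number is divided by 4, and the remainder decides the arm. "If the remainder is 0, the participant will be enrolled into dual tracing group"; remainders 1, 2 and 3 lead to control, CNs and ICG. No range or digit length is given for the numbers, and no block, stratum or cap is mentioned. The section ends: "The allocation is not blinded to surgeons or participants before performing procedure".

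The Study design section states the target ratio, "Participants were randomized into 4 groups at a 1:1:1:1 ratio", and describes the design in two successive sentences: "This is a prospective, unblinded, superiority testing, randomized controlled trial" and "A parallel group cluster randomized controlled trial with four arms will be conducted". The Study setting section gives one centre. The Sample size section works per individual and arrives at 129: "participants are finally required in each group, leading to a total of 516 participants".

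**The concern.** Three features of the rule and one label need attention.

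- **Ratio.** Remainders modulo 4 are equally likely only if the numbers come from a range whose size is a multiple of 4. A digit table can be read one, two or three digits at a time, and one digit at a time is not such a range.
- **Balance.** The rule is simple randomisation. Arm sizes are random, and so is the mix of total and distal gastrectomy. The Intervention section lists different node stations for the two procedures (4sa, 11d and 2 appear only under total gastrectomy), so procedure type plausibly affects the node count, which is the primary outcome.
- **Sequence.** A table read in order of inclusion, with a fixed decoding rule, can be read ahead by whoever holds it. In an open trial at one centre that would permit selective enrolment or deferral, and the article describes nothing to prevent it.
- **Label.** If clusters were really randomised, a sample size without a design effect and the ordinary t test named under Data analysis would not be valid.

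**Working it through.** **Inputs.** Difference 3 nodes, SD 8.6, one-sided alpha 0.05, power 0.80, dropout 20%, 129 per arm, 516 in total (Sample size); four arms at 1:1:1:1 (Study design); remainder of division by 4 (Randomization). The digit length is not stated and has to be assumed.

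**1. The plan's own figure.** Normal approximation: n = 2 × [8.6 × (1.645 + 0.842) / 3]² = 101.6, so 102. The one-sided two-sample t test with d = 3/8.6 gives 103, the stated figure. Then 103 / 0.8 = 128.75, so 129, and 4 × 129 = 516. The figure is reproduced, and it is an individual-level calculation with no cluster size, intracluster correlation or design effect.

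**2. Remainders by assumed range.** Expected arm size = 516 × share of the range with that remainder.

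| Numbers read | Remainders 0 : 1 : 2 : 3 | Dual / control / CNs / ICG |
|---|---|---|
| 00-99 | 25:25:25:25 | 129 / 129 / 129 / 129 |
| 000-999 | 250:250:250:250 | 129 / 129 / 129 / 129 |
| 0-9 | 3:3:2:2 | 155 / 155 / 103 / 103 |
| 1-9 | 2:3:2:2 | 115 / 172 / 115 / 115 |
| 1-99 | 24:25:25:25 | 125 / 130 / 130 / 130 |

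**3. Arm sizes when all arms have probability 1/4.** SD of one arm = √(516 × 0.25 × 0.75) = 9.8, so a 95% range of about 110 to 148. In 400,000 multinomial draws the smallest arm averaged 117 and the largest 141, and the two differed by 20 or more in 62% of draws. The exact probability that all four arms equal 129 is 0.00009.

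**4. Power after 20% dropout**, from Φ[3 / (8.6 × √(1/n₁ + 1/n₂)) − 1.645], taking 80% of each arm as evaluable:

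- Equal arms, 103.2 each: 80.5%.
- Simple randomisation with equal probabilities: average 80.4%, 95% range 77.2% to 83.2%.
- Single digits 0-9 (assumed; arms of 155 and 103 leave about 124 and 83): dual versus control 86%, dual versus ICG 79%, CNs versus ICG 72%.

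**5. Procedure type.** The share p having total gastrectomy is not in the document. The SD of the difference in that share between two arms of 129 is √(2p(1 − p)/129): 5.0 percentage points at p = 0.2, 6.1 at 0.4 and 6.2 at 0.5 (assumed values). At p = 0.4 a two-SD imbalance is about 12 points, so it moves the contrast by 0.12 × Δ nodes, where Δ is the difference in yield between procedures. Δ is not given either; Δ of 4 to 8 (assumed) gives about 0.5 to 1.0 node.

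**6. The cluster label.** Against it stand allocation of each participant in turn (Randomization), one centre (Study setting) and the individual-level sample size (step 1). No cluster is defined anywhere in the article.

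**The case against.** Simple randomisation is a valid way to run a 1:1:1:1 trial. The ratio is an allocation probability and 129 is a requirement, so neither promises exact counts, and the power cost of chance arm sizes is negligible (step 4). That stands. A reader might infer that the rule fails to deliver the stated ratio; with full two- or three-digit numbers it does deliver it in expectation. The 3:3:2:2 result depends on reading single digits, which the article neither states nor excludes. Under that reading dual versus control gains power.

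A reader might also infer, from the sentence that allocation is not blinded before the procedure, that the next assignment is unconcealed. The document does not support this. The sentence can mean only that an assignment is known once made, and that is unavoidable because CNs are injected the day before surgery. Openness after allocation is not lack of concealment before it. Custody of the list is also a detail that an article may leave to the full protocol, and any pre-generated list can be read by its holder.

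Chance imbalance in procedure type is not bias. It is part of the sampling error, which is 8.6 × √(2/103) = 1.2 nodes for a difference at 103 per arm. Unrestricted allocation also has a real merit in an open trial: past assignments say nothing about the next one, whereas blocks make some assignments near a block end guessable.

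What the objection does not remove is that the article spells out its algorithm and leaves open the one element that determines whether it is fair, and that the cluster label is contradicted by the rest of the text.

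**Conclusion.** The point holds as a correction worth making, not as a fatal flaw.

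- **Certain:** the rule is unrestricted and its number range is not fixed, so 1:1:1:1 holds only on average and only for ranges that are multiples of 4. The word cluster is wrong for this trial.
- **Negligible:** the average power loss from chance arm sizes, about 0.1 percentage point.
- **Conditional on single digits being read:** 3:3:2:2, with CNs versus ICG at about 72% power against about 80% with equal arms, both after dropout.
- **Not sized by the document:** the effect of imbalance in procedure type, which rests on an assumed share and an assumed difference in yield. It is a matter of precision and credibility, not bias.
- **Inference only:** the risk of reading the table ahead. The article describes no safeguard; it does not say that allocation is unconcealed.

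A reader might conclude from the cluster label that the sample size and t tests are invalid. That would follow only if clusters were randomised, and everything else in the article describes individual randomisation. It is a mislabel.

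**What to change.** For patients not yet allocated, replace the remainder rule with a computer-generated 1:1:1:1 list in permuted blocks of randomly varying size, stratified by planned gastrectomy type (total or distal), with block sizes not disclosed to those who recruit. Have the list held by existing staff who do not enrol patients, and release each assignment only after consent and eligibility are recorded. Include the stratum in the primary analysis of node count. State which number range has been used so far; patients already randomised keep their arm. In the Study design section, delete the word cluster and state that the individual patient is the unit of randomisation.

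The cost is a minor amendment and a new list. Recruitment was planned from 01 August 2023 to 30 July 2025, so the change may reach only part of the sample. Institutional Review Board approval is needed if it counts as significant under the Protocol amendments section. Planned procedure type must be recorded before allocation. Blocking brings slight predictability near block ends, which varying the block size limits but does not abolish. No extra patients are needed.

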### Outcome

The primary outcome is the total number of retrieved LNs. The secondary outcomes include positive rate, false positive rate, negative rate, false negative rate, number of metastatic LNs, rate of LN metastasis, relationship between LN metastasis and dual staining, morbidity and mortality, 3-year disease-free survival rate, 3-year overall survival rate, 3-year recurrence rate, postoperative recovery, duration of surgery, changes in body weight, intraoperative blood loss, intraoperative mortality, incision length, body temperature, and changes in lab parameters (albumin, prealbumin, hemoglobin, white blood cells, C-reactive protein, etc.).

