### Data analysis

Database will be established using Epidata 3.0, and statistical analysis will be performed using SPSS 18.0. This trial uses differential testing; a *p*-value less than 0.05 will be considered statistically significant, and the confidence intervals for the parameters will be estimated as 95%.

In this trial, validity analysis based on MITT (modified intention to treat) analysis will be conducted. The primary and secondary outcomes will be analyzed with both MITT and PP (per protocol) analysis. Conclusion of MITT analysis will be the primary analytical method, and if the conclusions of PP analysis and MITT analysis are consistent, the credibility of the conclusions can be improved. SP (safety population) analysis will be used to analyze laboratory evaluations, adverse events, and adverse reaction data. SP will be defined as the denominator for the incidence of adverse reactions.

Descriptive statistics will be used to systematically describe primary and secondary outcomes. Means, standard deviations, and confidence intervals will be presented based on data from the control group and intervention groups. Frequency distributions, percentages, medians, and mean rank order will be presented based on quantitative data and rank data. Positive rates, positive number, and total number of retrieved LNs will be presented based on qualitative data. The number of events, number of missingness, median survival time, and survival rate will be presented based on survival data. Efficacy analysis will be performed on data following descriptive statistics. This study utilizes Pearson chi-square test for qualitative data, *t* test for quantitative data, Wilcoxon rank sum test for ranked data, Log-rank test for univariate analysis and Cox regression model for multivariate analysis of survival data, and two-tailed test for safety indicators and incidence of adverse reactions.

Abnormal values will be judged when the observed value is greater than P75 or less than P25, and 3 times more than the interquartile range defined as P75 subtracts P25. Sensitivity analysis will be performed on the abnormal data, and the data will be retained if results are not contradictory. If there is a contradiction, specific analysis will be conducted.

Subgroup analysis will be performed to identify risk factors for the prognosis according to the specific circumstances of the data.

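### Changes in body weight and laboratory values are to be compared by an unadjusted t test, which is valid but usually less precise than a model that includes the preoperative value

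*Protocol article*

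**What the plan says.** The Outcome section of the protocol article defines two kinds of secondary outcome as changes: "changes in body weight" and "changes in lab parameters (albumin, prealbumin, hemoglobin, white blood cells, C-reactive protein, etc". A change can be computed only if each patient has a preoperative value.

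The Data analysis section assigns one method to each type of data. For continuous and ordinal data it names a *t* "test for quantitative data, Wilcoxon rank sum test for ranked data". The only model with covariates is for time-to-event outcomes: "Cox regression model for multivariate analysis of survival data". The section also states that "SP (safety population) analysis will be used to analyze laboratory evaluations, adverse events, and adverse reaction data" and specifies a "two-tailed test for safety indicators and incidence of adverse reactions". These last two provisions settle the analysis set and the sidedness of the test. Neither brings in the baseline value.

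Read together, the two sections specify an unadjusted *t* test on change for these outcomes.

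**The concern.** A *t* test on change subtracts the whole preoperative value, which amounts to fixing its regression coefficient at 1. The coefficient that the data would support is the correlation times the ratio of the postoperative to the preoperative standard deviation, and this need not be 1. Where it is not, two things follow. The confidence interval for the arm difference is wider than it need be. The estimate also moves with whatever baseline difference chance has produced between the arms.

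What is at stake is the precision of the weight and laboratory comparisons between tracer arms. ANCOVA uses the same data and estimates the coefficient.

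**Working it through.** **Inputs.** From the Sample size section: standard deviation 8.6, difference 3, α 0.05 one-tailed, power 0.8, 103 per group, 20% dropout, 129 per group, 516 in total. From Data analysis: two-tailed testing for safety indicators. The correlation ρ between pre- and postoperative values, and the standard deviations SD_pre and SD_post, are not in the documents. They are assumptions below, shown over a range.

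**The plan's own figure.** The one-sided *t*-based calculation at d = 3/8.6 gives 102.30, hence 103. Then 103/0.8 = 128.75, hence 129, and 4 × 129 = 516. The stated size reproduces. It is set on the lymph-node count, which has no baseline value. The protocol states no size or power for the change outcomes.

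**General comparison of the two methods.**
- Var(change) = SD_post² + SD_pre² − 2ρ·SD_pre·SD_post
- Var(ANCOVA residual) = SD_post²(1 − ρ²)
- Difference = (SD_pre − ρ·SD_post)²

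The difference is never negative. It is zero only when SD_pre/SD_post = ρ, that is, when the true slope ρ·SD_post/SD_pre equals 1. Apart from one degree of freedom, ANCOVA cannot lose precision.

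**Equal standard deviations (assumed).** The variance ratio of ANCOVA to change score is (1 − ρ²)/[2(1 − ρ)] = (1 + ρ)/2. Take an effect that the change score detects with 80% power, two-sided 5%. Power under ANCOVA is Φ[(1.960 + 0.8416)/√ratio − 1.960].

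| ρ (assumed) | Variance ratio | Power, ANCOVA |
|---|---|---|
| 0.3 | 0.65 | 93.5% |
| 0.5 | 0.75 | 89.9% |
| 0.7 | 0.85 | 86.0% |
| 0.8 | 0.90 | 84.0% |
| 0.9 | 0.95 | 82.0% |
| 0.95 | 0.975 | 81.0% |

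At one-sided 5% the first four figures are 92.5%, 89.0%, 85.4% and 83.5%. A simulation of 4,000 trials with 103 per arm gave change score versus ANCOVA power of 78% and 93% (ρ 0.3), 80% and 90% (ρ 0.5), and 80% and 83% (ρ 0.8).

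**Unequal standard deviations (assumed; SD_post set to 1).**
- SD_pre 0.5, ρ 0.5: Var(change) = 1 + 0.25 − 0.50 = 0.75 and ANCOVA = 1 − 0.25 = 0.75. There is no gain.
- SD_pre 0.2, ρ 0.3: Var(change) = 1 + 0.04 − 0.12 = 0.92 and ANCOVA = 0.91. Power goes from 80% to about 80.4%.
- SD_pre 0.2, ρ 0: 1.04 against 1. Power goes to about 81.5%.
- SD_pre 0.2, ρ 0.5: Var(change) = 1 + 0.04 − 0.20 = 0.84 and ANCOVA = 0.75, a ratio of 0.893. Power = Φ(2.8016/0.945 − 1.960), about 84%.

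The size of the gain therefore depends on how far SD_pre/SD_post lies from ρ, not on ρ alone.

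**Chance imbalance.** With equal standard deviations the change-score estimate shifts by −(1 − ρ) times the observed baseline difference. Simulated slopes were −0.70, −0.51 and −0.21 at ρ 0.3, 0.5 and 0.8, against about 0 for ANCOVA. With 103 per arm the standard error of a baseline difference is √(2/103) = 0.14 SD, so a difference beyond 0.2 SD arises in about 15% of pairwise comparisons for any one marker. At ρ 0.5, an imbalance of 0.2 SD moves the estimate by 0.5 × 0.2 = 0.10 SD. Over all simulated trials the mean bias was about zero, and type I error was 4.6% to 5.0% for both methods.

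**The case against.** The strongest objection is that this is detail for the statistical analysis plan. The Data analysis section is a short list of tests by data type in a condensed article, the analysis plan is not shown, and it is only by joining two sections that one finds raw changes being *t*-tested. This limits the weight of the point but does not remove it: the article names a method for all quantitative data, and adjustment in an analysis plan would depart from that method.

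Four stronger readings are tempting, and the documents do not support them.

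- A reader might infer that the *t* test on change is biased. It is not: under valid randomisation its average bias is zero and its type I error is near 5%. Only the estimate conditional on the imbalance that occurs is shifted.
- A reader might infer that raw change over-subtracts the baseline whenever the correlation is below 1, so that every listed outcome would gain 4 to 13 points of power. That requires equal standard deviations, which the documents do not give. Untransformed C-reactive protein and white cells may well vary more after surgery, and body weight may have a correlation near 0.95.
- A reader might blame the allocation method, in which "according to the order of inclusion, each participant will be allocated a random number" with no blocking. Blocking controls arm sizes and would not by itself balance baseline albumin or weight.
- A reader might infer that these outcomes carry the comparison of recovery. Outcome lists postoperative recovery separately, and Postoperative parameters describes it by ambulation, diet, tubes, drainage and hospital stay.

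**Conclusion.** The point holds as a minor matter of efficiency. The protocol specifies an unadjusted *t* test for outcomes whose definition already requires a baseline value, and ANCOVA would be at least as precise, apart from one degree of freedom.

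The benefit ranges from nothing to about 13 percentage points of power over the cases tabulated. The upper end rests on equal standard deviations before and after surgery and a correlation of 0.3. The 80% starting point is hypothetical, since the plan sets no target effect for these outcomes. The validity of the trial, the primary outcome and the total of 516 are untouched.

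**What to change.** In Data analysis, for body weight and each laboratory change outcome, replace the *t* test on change with a linear model of the postoperative value on allocated arm and the patient's preoperative value. Log-transform skewed markers such as C-reactive protein first. Report adjusted arm differences with 95% confidence intervals, and keep raw changes as description.

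Name the time points to be compared and fit the model at each. This is needed because laboratory values are collected in hospital (Postoperative parameters) and blood tests recur at 11 follow-up visits (Table 1), so a reference to the postoperative value alone would leave the analysis undefined.

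The cost is a sentence or two of text. The model uses only values that the change outcomes already require, runs in the SPSS software already named, and needs no further patients or visits. It should be written in before the data are analysed, so that the adjustment is not a post hoc choice.

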### Eligibility of surgeons

An experience of at least 100 laparoscopic radical gastrectomy is required for surgeons involved in this study.

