### Intervention

#### Preoperative administration of CNs

Following enrollment, surgery should be performed within 2 weeks (including day 14). In addition to routine preoperative management, peritumoral submucosal CNs injection is administered 1 day before surgery in CNs group and dual tracer group. Carbon nanoparticles suspension injection (Chongqing Lummy Pharmaceutical Co., Ltd.) is diluted into 25 mg/ml with saline and then injected using “sandwich method.” Briefly, approximately 0.5 ml saline is firstly injected into the submucosal layer for mucosal elevation. Then, 0.2 ml CNs is injected. Finally, 0.5 ml saline is injected again to prevent leakage of CNs. This injection is performed at both proximal and distal sides of tumor under gastroscopy.

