#### Intraoperative lymph node localization and dissection

After anesthesia, ICG (Dandong Yichuang Pharmaceutical Co., Ltd.) powder is diluted into 2.5 mg/ml with saline and then injected into subserosal layer using “hexa-site” method in the ICG group and dual tracer group [18]. Briefly, the injection is performed at 3 sites along the lesser curvature (first branch of left gastric artery, angular and first branch of right gastric artery). Similar injection was repeated along the greater curvature.

A near-infrared (NIR) fluorescence imaging system (PINPOINT, NOVADAQ, Mississauga, ON, Canada) is used to obtain near-infrared fluorescence imaging during surgery. It provides high-definition white light visual field, near-infrared fluorescence visual field, and ICG-specific SPY visual field as well as merged visual field. LN dissection in the ICG group and dual tracer group is performed under the fluorescent laparoscope.

The standard sequence of LN dissection is as follows: (1) total gastrectomy: No. 6 → No. 7, 9, 11p → No. 8a, 12a, 5 → No.1 → No. 4sb → No. 4sa, 11d → No.2; (2) distal subtotal gastrectomy: No. 6 → No. 7, 9, 11p → No. 3, 1 → No. 8a, 12a, 5 → No. 4sb. Selective dissection of No.10 LNs is performed when (1) the primary tumor is located in the middle/upper stomach and invaded a large extent, (2) preoperative radiology suggests splenic lymphadenopathy, (3) significant fluorescent signal of No. 10 LNs, and (4) black stained No. 10 LNs by CNs. Surgical area is routinely inspected for possible residual fluorescent LNs or black-stained LNs, and additional dissection will be performed if necessary. D2 + LN dissection will be performed if fluorescent or black-stained LNs (such as No. 10 or No. 14v) are observed outside D2 region.

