##### Surgical parameters

The following information will be recorded: (1) name of leading surgeon; (2) procedure duration; (3) procedure type especially digestive tract reconstruction method; (4) incision length; (5) whether converted to open surgery and reason; (6) intraoperative blood loss; (7) blood transfusion volume; (8) tumor location; (9) maximum diameter of tumor size; (10) whether distant metastasis is observed and, if any, the location of metastasis; (11) proximal and distal resection margin, radical cure (R0/R1/R2); (12) intraoperative complications including vascular injury, organ injury, tumor rupture, hypercapnia, emphysema, subcutaneous emphysema, air embolism, allergic reactions, etc.; (13) intraoperative death if occurs.

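### Nothing in the article prevents the choice of lead surgeon, or of total versus distal resection, from depending on an allocation the surgeons already know

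*Protocol article*

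**What the plan says.** All places are in the protocol article.

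- **Study design:** "This is a prospective, unblinded, superiority testing, randomized controlled trial".
- **Randomization:** "according to the order of inclusion, each participant will be allocated a random number", and the remainder after division by 4 gives the arm. This is simple individual allocation with no surgeon or procedure stratum. The section adds that "The allocation is not blinded to surgeons or participants before performing procedure".
- **Preoperative administration of CNs:** the operation may take place up to 14 days after enrolment, and "peritumoral submucosal CNs injection is administered 1 day before surgery in CNs group and dual tracer group".
- **Eligibility of surgeons:** the whole section is one sentence, "An experience of at least 100 laparoscopic radical gastrectomy is required for surgeons involved in this study". It speaks of surgeons in the plural.
- **Surgical parameters:** "name of leading surgeon" is the first item recorded. The lead surgeon is mentioned nowhere else.
- **Intraoperative lymph node localization and dissection:** total and distal gastrectomy have different station sequences. Stations 4sa, 11d and 2, for example, are listed only for total gastrectomy. Also, "LN dissection in the ICG group and dual tracer group is performed under the fluorescent laparoscope".
- **Data analysis:** quantitative outcomes are compared by t test. No surgeon or procedure term is stated.

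**The concern.** Randomisation balances what is settled before the draw. It does not balance what is decided afterwards by people who know the result. Here the arm can be known while the theatre list is still open, and in two arms the preoperative injection makes it plain the day before. If several surgeons share the work, cases could drift by arm. Surgeons more used to the fluorescence system might take the cases that use it, for instance. The comparison would then be partly one of operators.

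The type of resection raises the same question in a weaker form. It sets which stations are dissected, and nothing requires the plan to be recorded before allocation.

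The planned difference is only 3 nodes against a standard deviation of 8.6, so a modest operator effect is not negligible. If surgeon or procedure were in fact chosen after allocation, each would be a post-randomisation variable. Adjusting for the value recorded at operation would then not be a clean repair. That is the reason for fixing both before the draw.

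**Working it through.** **1. The plan's own figure.** Inputs from Sample size: one-sided α = 0.05, power 0.80, SD 8.6, difference 3, dropout 20%.

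- Normal approximation: n = 2 × [(1.645 + 0.842) × 8.6/3]² = 101.6, so 102 per arm.
- Noncentral t with d = 3/8.6 = 0.349: 103 per arm.
- 103/0.8 = 128.75, so 129 per arm, and 4 × 129 = 516.

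The stated 103, 129 and 516 reproduce one-sided, and this point does not change them.

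**2. Standard error of a two-arm difference.** SE = 8.6 × √(2/103) = 1.198 nodes. Power with no bias is Φ(3/1.198 − 1.645) = 0.80.

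**3. Operator bias.** Let D be the gap in mean yield between higher- and lower-yield surgeons, and q the difference between two arms in the share of cases done by the higher-yield surgeons. Then bias b = D × q.

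The document gives neither quantity. For illustration I assume D from 3 to 5 nodes and q from 0.10 to 0.30.

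- If the bias favours the tracer arm, the one-sided error rate is 1 − Φ(1.645 − b/1.198).
- If it runs against the tracer arm, power is Φ((3 − b)/1.198 − 1.645).

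| D | q | b (nodes) | b as share of 3 | Error rate if favourable | Power if adverse |
|---|---|---|---|---|---|
| 3 | 0.10 | 0.3 | 10% | 0.082 | 0.73 |
| 3 | 0.20 | 0.6 | 20% | 0.126 | 0.64 |
| 5 | 0.20 | 1.0 | 33% | 0.209 | 0.51 |
| 5 | 0.30 | 1.5 | 50% | 0.347 | 0.35 |

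**4. Chance imbalance is a separate matter.** If a higher-yield group does half the cases, the standard deviation of q under simple randomisation is √(2 × 0.25/103) = 0.07. Imbalance of that kind is random and is covered by the t test's error rate. Only a shift caused by knowledge of the arm is bias.

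**5. What adjustment could gain in precision.** With two equal-sized surgeon groups, the between-surgeon variance is D²/4. That is 2.25 for D = 3 and 6.25 for D = 5. Against 8.6² = 73.96, and if 8.6 includes surgeon variation, this is 3.0% to 8.5% of the variance. The gain is small but real.

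**The case against.** **Recording is not choosing.** The Surgical parameters list shows when the name is recorded, not when the surgeon is assigned. A reader might infer that surgeons are picked after allocation, but the article does not say so. If each patient already has a surgeon at admission, recording the name at operation is ordinary practice and adjusting for it is valid. This stands. The point is that the text leaves the route open, not that anyone uses it.

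**The surgeon criterion is not limited to conventional surgery.** A reader might take it to qualify surgeons for the control operation only. It does not say that. Study design uses the term laparoscopic radical gastrectomy for all four arms, so tracer-guided cases could count toward the 100. At most, the section names no separate threshold for tracer experience. Operator training is something an article may leave to the full protocol, so no case minimum is asked for here.

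**A condensed article may omit rostering rules.** This is fair and limits how firmly the point can be put. But the article does state open allocation before the procedure, and it does state a test with no surgeon or procedure term. The change proposed also alters the enrolment step and the analysis, so it is more than writing down a missing detail.

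**There are safeguards.** The dissection sequence is standardised, the whole procedure is filmed, and certain incomplete dissections lead to withdrawal. These limit variation in technique. They do not govern who operates. Study design also calls the trial cluster randomised, but no cluster is defined and Randomization allocates individuals, so that phrase gives no protection.

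**Resection type depends mainly on tumour location.** Location is a baseline feature that randomisation balances in expectation, and it is recorded. This part of the concern is therefore the weaker one. Recording the plan beforehand costs almost nothing and gives a valid covariate.

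**Conclusion.** The point holds in limited form. Surgeons know the arm before operating, up to 14 days may pass between enrolment and surgery, more than one surgeon may operate, and nothing stated ties operator or planned resection to a moment before the draw. The stated analysis does not account for either.

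Neither the size nor the direction of any bias can be taken from the document. The range of 0.3 to 1.5 nodes rests wholly on assumed surgeon differences and assumed routing. It should not be read as saying that the trial's error rate is 8% to 35%. That is the result only if the imbalance favours the tracer arm. If it runs the other way, for example because operators are less practised with a tracer, the effect is lost power (0.73 to 0.35 over the same range). No net direction is established.

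The change is still worth making. It closes an avoidable route to bias in an operator-dependent outcome at little cost, and it can be applied only before each patient is allocated.

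**What to change.** **Randomization:** require the lead surgeon and the planned resection (total or distal) to be entered on the enrolment form before the random number is drawn. The named surgeon operates whatever the arm. Any swap of surgeon is logged with its reason.

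**Data analysis:** replace the plain t test for node count with a linear model containing arm, the surgeon named before allocation and the resection planned before allocation. Use the pre-allocation values even where the actual surgeon or procedure differed.

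**Cost:** two form fields, a swap log and one changed sentence in the analysis section. The sample size stays as it is. The downside is slightly less freedom in theatre rostering. Surgeons will still know the arm while they operate. The change removes choice of operator by arm, not every effect of an open design.
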